## Protocol overview

With current knowledge, it is difficult to set a randomized trial between a population undergoing VT-ART (e.g., in the compassionate setting often applied for patients proposed for such an innovative procedure) and a population not undergone to that. Randomizing a patient’s accrual to VT-ART instead of the conventional option implies that some patients would skip a conventional procedure in favor of a procedure still considerate at least still non-standard, although promising. Multiple, reliable phase I and phase II trials are not available, although case series and at least one phase I/II trial have investigated VT-ART efficacy (1).

Finally, it would be difficult to define two balanced treatment arms that are suitable for a clinical randomized comparison, since patients undergoing VT-ART would have either already received RFA or are unable to receive it, and they have already undergone other standard treatments. On the other hand, setting a single-arm trial would test less efficiently the clinical of VT-ART and could imply the adoption of VT-ART only for worse clinical case presentations.

This multicenter observational study will evaluate the efficacy and safety of VT-ART. Our trial will enroll patients with optimized medical therapy, in whom endocardial and/or epicardial RFA is either unfeasible or fails to control VT recurrence. The trial is set as observational since it indirectly comparing VT-ART with a conventional procedure (i.e., RFA).

Each patient recruited for VT-ART will be profiled according to a predefined list of characteristics that will be circulated within the centers participating to the consortium to collect other patients with a similar profile, not having undergone VT-ART, for final analysis.

The peculiar setting of our trial will avoid precluding VT-ART to patients possibly taking advantage of such a therapeutic option; moreover, it will compare VT-ART with retrospective series not having receive VT-ART anyway. Furthermore, this approach will retrieve otherwise sporadic data about single or limiter case series of each center joining the consortium. This trial is not strictly investigational but can add notable scientific information to the current scenario.

The multicenter setting of this study will allow for faster recruitment of the sample size.

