### Statistical considerations and sample size for matched pair analysis

A descriptive analysis will summarize the total number and stratification of patients with RFA and VT-ART.

We will perform a comparative analysis between RFA and VT-ART in patients with structural heart disease and refractory VT. Each patient who will be treated by VT-ART will be compared with two patients in the control group treated with RFA and best standard care but without VT-ART, on the basis of the following matching factors: Etiology of cardiomiopathy (ICM, NICM, and ACM), ventricular arrhythmia presentations (sustained ventricular tachycardia; incessant sustained ventricular tachycardia; and electrical storm), diagnostic tools used for scar definition (CT, MR, EAM, and ECG), arrhythmogenic focus anatomical intracardiac location (on the basis of VE exit by ECG and by activation map of VT), TA volume (endocardial electroanatomic substrate mapping area/volume in all cases; and epicardial mapping area/volume in case of 3D epicardial electroanatomic substrate mapping), heart volume, heart-to-TA volume, rate number of previous RFA attempts, type of previous RFA attempts (endocardial and epicardial), time (in days) between the first RFA attempt and VT-ART, time (in days) between the last RFA attempt and VT-ART, previous percutaneous stellate ganglion blockade, time (in days) between the percutaneous stellate ganglion blockade and VT-ART previous use of amiodaron, NYHA group, LVEF, BMI, age, and gender.

As mentioned, applied matching factors are summarized in Table 2.

Continuous data will be expressed as mean ± standard deviation, as appropriate, for all variables collected from the entire population or specific subgroups. A comparative analysis for subsequent levels of qualitative variables through the chi-square test and quantitative variables (scores on quality of life) with the *T*-test will be performed.

Non-parametric tests will be provided where the population distribution does not have a known form (normal Gaussian).

The differences in baseline and follow-ups between the same group will be analyzed with repeated measures approach: using the Friedman test and MANOVA for continuous variables and McNemar or Cochran’s *Q*-tests for categorical ones.

The significance of the tests is fixed with *p* < 0.05.

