#### Sample size

The calculation of the sample size considered followed assumptions:

-A total of 95% confidence level;-The drop-out rate of 10%;-Expected difference between the two treatments for 3-month and 6-month VT burden in terms of overall response rates: 20% higher in arm including VT-ART compared to the control group;-Power of 80%.

To improve clinically adequate balancing, we will enroll two matching paired patients in the group not undergoing VT-ART for each patient who undergoes VT-ART in a 2:1 ratio, favoring a larger proportion of patients not undergoing the innovative procedure (i.e., VT-ART).

Under these hypotheses, to detect a 20% improvement in the VT burden control rate in the VT-ART group vs. the control group, we calculated the sample size (in a 2:1 ratio) upon enrolling 149 patients: 100 in the non-exposed control group and 49 in the VT-ART group. Progressively, on a multicentric basis supervised by the promoting center in the VT-ART consortium, for each VT-ART patient enrollment, a matched pair patient profile according to the predefined features will be shared with the consortium to enroll two similar patients who have not undergone VT-ART. For enrollment into the control group, recruitment of clinical cases from retrospective case series within the multicentric consortium will also be allowed, with the only condition to be not earlier than 5 years from the enrollment of the matched pair patient in the VT-ART group (to avoid the possible influence of a too early approach for standard procedures).

All statistical analyses will be performed using SPSS^®^ version 25.0 software (©Copyright IBM Corporation 1994, 2017).

Due to the potential difficulty of enrolling the patients through the complete match of all matching factors, a protocol rule will be applied through patient’s collection.

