Once the planned number of the innovative procedure will be collected, the trial will put a 6-month observation time. If after that, 60% of the planned conventional arm patients will be collected (by all matching factors and in a 2:1 ratio), a further 3 months will be provided to reach the planned accrual. If that would have not been the case, then the patient’s enrollment will be allowed by mandatory matching factors only (only beyond that point). The detail of “mandatory matching factors” is reported in Table 2. The final analysis will be performed by the whole group and subgroup analyses, discriminating patients collected through “all matching factors” and by “mandatory-only.”

The final analysis will not be performed at all if less than a 1:1 ratio (conventional: Innovative group) of patient’s enrollment will be collected, and the study will be closed.

The final analysis will be performed specifying that the planned accrual is not met if at least a 1:1 ratio (conventional: Innovative group) enrollment will be accomplished; results will be explored and cautiously evaluated.

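### The 1:1 floor for running the final analysis is a ratio of group totals, so it does not ensure that each analysed VT-ART patient has a matched control

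*Protocol article*

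**What the plan says.** Three parts of the protocol article bear on this.

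- **The comparison is defined by matched set.** Statistical considerations and sample size for matched pair analysis: "Each patient who will be treated by VT-ART will be compared with two patients in the control group", chosen on the matching factors. Methods/design likewise describes a matched pair analysis built on the characteristics of the VT-ART patients. Sample size repeats the two-for-one matching and plans "upon enrolling 149 patients: 100 in the non-exposed control group and 49 in the VT-ART group".
- **Controls are chased after the VT-ART group is full.** Sample size: "Once the planned number of the innovative procedure will be collected, the trial will put a 6-month observation time". The check at that point is whether "60% of the planned conventional arm patients will be collected (by all matching factors and in a 2:1 ratio"). If so, 3 more months are allowed; otherwise enrolment on the mandatory factors alone is opened.
- **The decision to analyse uses group totals.** Sample size: "The final analysis will not be performed at all if less than a 1:1 ratio (conventional: Innovative group) of patient’s enrollment will be collected". At or above that ratio the analysis goes ahead: "The final analysis will be performed specifying that the planned accrual is not met if at least a 1:1 ratio (conventional: Innovative group) enrollment" is accomplished, with the results to be read with caution. On who is analysed: "The final analysis will be performed by the whole group and subgroup analyses", the subgroups being patients matched on all factors and on mandatory factors only.

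The Follow-up section restricts the final analysis to patients with data at the scheduled time points. That is a condition on each patient's data and does not require a match.

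**The concern.** In a design of one VT-ART patient to two controls, the number of controls does not tell you how many VT-ART patients have one. Sixty controls can serve 30 VT-ART patients or all 49. The rule that decides whether the comparison is run looks only at the total, so it is in the wrong unit for the design it governs.

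This matters because matching is the only control of confounding that the article states for a non-randomised comparison. A VT-ART patient for whom the consortium finds no similar RFA patient may have an unusual profile. If such patients are pooled with the rest, part of the VT-ART group is compared with controls chosen to resemble other people. The between-group tests that the article names (chi-square, t-test and non-parametric alternatives) take whole groups and would not drop a patient for lack of a match.

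This is separate from whether the standard errors respect the matching. It concerns patients who belong to no matched set.

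**Working it through.** **Inputs from the article (Sample size):** 49 VT-ART patients, 100 controls, two controls per VT-ART patient, a check at 60% of planned controls, and a floor of 1:1.

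**The plan's own figure.** The total of 149 cannot be firmly reproduced, because no control response rate is given. The usual two-proportion formula (two-sided 5%, 80% power, 2:1, no continuity correction) at an assumed 10% v 30% gives 44 VT-ART patients; 44/0.9 = 48.9, so 49, and 3 × 49 = 147, close to 149. At 50% v 70% it gives 71, and 79 after drop-out, a total of 237. The point here does not depend on that calculation.

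**Step 1: how many VT-ART patients can lack a control.** With C controls and at most two per set, the fewest VT-ART patients with any control is C/2 rounded up; the most is the smaller of C and 49.

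| Controls | Ratio to 49 | Passes 1:1? | Unmatched, worst case | Unmatched, best case |
|---|---|---|---|---|
| 49 | 1.00 | yes | 49 − 25 = 24 (49%) | 0 |
| 60 (60% of 100) | 1.22 | yes | 49 − 30 = 19 (39%) | 0 |
| 74 | 1.51 | yes | 49 − 37 = 12 (24%) | 0 |
| 98 or 100 | 2.00 or 2.04 | yes | 0 | 0 |

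The worst case is what filling sets in pairs produces. The check at 60% counts controls in just that way, 60/2 = 30 complete sets, and 60:49 already exceeds the floor. The rule gives the same answer for the worst and best columns.

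**Step 2: what pooling the unmatched patients would do (illustration; D is assumed).** If their outcome rate differs by D from that of the matched VT-ART patients, the crude VT-ART rate shifts by (unmatched/49) × D:

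- 49 v 60: 19/49 × D = 3.9 points for D = 10, and 7.8 points for D = 20.
- 49 v 49: 24/49 × D = 4.9 points for D = 10, and 9.8 points for D = 20.

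The shift takes the sign of D. The design difference is 20 points.

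**Step 3: effect on a whole-group chi-square test (same illustration).** Assume a 50% control rate, no true effect, independent outcomes and D = 20 points. Exact enumeration of the two-sided 5% test gives a false-positive rate of 12.3% at 49 v 60 and 16.8% at 49 v 49. With D = 0 the rates are 4.9% and 5.4%.

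**Step 4: the price of restricting to matched patients.** Assume 50% v 70% and D = 0. Power of the unpaired test is about 57% at 49 v 60 and about 44% at 30 v 60. If the unmatched patients do worse by 10 points, whole-group power at 49 v 60 falls to about 40%, below the matched-only figure.

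**The case against.** The strongest reply is that nobody unmatched was meant to be analysed. The article defines 2:1 as two controls for each VT-ART patient, so 1:1 may mean one for each. Methods/design speaks of matched pair analysis, in which a patient without a control has no place. The whole group may mean only the two matching routes pooled, since the subgroups set against it are both matched. The article names no test for the survival endpoints, and the handling of unmatched patients could sit in the full protocol or SAP. This stands as far as it goes: inclusion of unmatched patients is inferred, not stated. It does not rescue the rule, because the floor is written as one group's enrolment against the other's, and nothing shown converts it into a count of sets.

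Second, the plan has its own remedies. Falling short opens matching on the eight mandatory factors, and reaching 60% opens 3 more months. Both make 19 or 24 unmatched patients less likely. Neither guarantees a control for each patient, and the 1:1 clause exists because accrual may still fail.

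Third, the size of the bias is assumed. That is right. A reader might infer that VT-ART is bound to look worse, and point to the remark in Protocol overview that a single-arm trial "could imply the adoption of VT-ART only for worse clinical case presentations". That remark concerns what a single-arm design might lead to, not the prognosis of patients without a match. A match can also fail because a retrospective control lacks mapping or volume data, which need not be prognostic. The document supports neither a direction nor a size.

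**Conclusion.** The point holds as a defect in a stated rule. The article fixes its go/no-go floor on group totals while defining the comparison by matched set, so the floor can be met with anything from none to 24 of 49 VT-ART patients unmatched. The upper figure is a bound that assumes controls placed in pairs and the fallback failing to fill the gap; it is not a forecast.

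It would go too far to say that the plan will put half of the VT-ART group into the comparison without controls, or that its result will be biased against VT-ART. Bias requires that unmatched patients are analysed, which the wording allows but does not state, and that their prognosis differs, which cannot be checked from the document. The 8-point shift and the false-positive rates above rest on an assumed 20-point difference, and the latter also on an assumed 50% control rate. The problem arises only if controls fall short, an outcome the article itself plans for.

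**What to change.** In the accrual rules under Sample size:

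1. State the 1:1 and 2:1 thresholds as the number of VT-ART patients with at least one and at least two matched controls.
2. Base the main between-group comparison on those matched sets: a VT-ART patient enters with at least one matched control, and a control enters only with its index VT-ART patient.
3. Report unmatched VT-ART patients separately: number, baseline profile, outcomes and safety.
4. Keep the whole-group comparison as a sensitivity analysis.

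If the sponsor already intends 1:1 to mean one matched control for each analysed VT-ART patient, writing that down settles the first two items.

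The cost is a few sentences of amendment, with no new patients or data. If controls fall short, the main comparison uses fewer VT-ART patients (for example 30 instead of 49), and its conclusion applies only to patients for whom a comparable RFA patient exists. Power is lower if unmatched patients have the same prognosis: about 44% against 57% under the assumed 50% v 70%.

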### Toxicity evaluation

Radiotherapy-related toxicity will be defined using the Common Terminology Criteria for Adverse Events (CTCAE) v5.0. All adverse events, regardless of the toxicity grade and all-cause mortality, will be reported in the final study. Patients will be re-evaluated at 2 years of follow-up for late-onset toxic effects.

The secondary safety endpoints for VT-ART include the evaluation of all adverse events, which are classified as follows:

•Acute, during the patient’s hospital stay;•Subacute, in the first 90 days from discharge;•Chronic, 6–12 months following discharge.

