### Follow-up

Follow-up will be conducted for 36 months after treatment administration.

Patients prospectively enrolled within the consortium and treated by VT-ART will undergo ICD interrogations for up to 36 months after enrollment.

After a blanking period of 3 months, regular ICD interrogations [with intracardiac electrogram (EGM) storage of VT/VF or appropriate shock or ATP] will be prospectively collected for patients treated by VT-ART at 6, 9, 12, 18, 24, 30, and 36 months after the VT-ART procedure.

The ICD interrogation will collect the events along the last 3 months ahead of each follow-up evaluation.

Patients prospectively enrolled within the consortium and treated by RFA will undergo the same follow-up schedule if possible according to the clinical patient’s need and compliance.

Patient data retrospectively collected within the consortium and treated by either RFA or VT-ART will be retrospectively extracted at the same time points of prospective follow-up.

The final analysis will be performed only for patients with available data for the mentioned time points, either retrospectively or prospectively collected.

Quality of life will be assessed before the procedure (for prospectively enrolled patients candidate to VT-ART and RFA) and at 3, 6, and 12 months after therapy. Improvement in the patient’s quality of life will be assessed compared to the pre-treatment period using the SF36 scale.

Patient follow-up will thus, briefly, include:

•ICD interrogation (with EGM storage of VT/VF) at 6, 9, 12, 18, 24, 30, and 36 months from treatment.•A total of 12-lead ECG at 3, 6, and 12 months.•Echocardiography at 3, 6, and 12 months.•QoL assessment using the SF36 scale (7) will be performed at 3, 6, and 12 months for patients undergoing VT-ART.•QoL assessment using the SF36 scale will be performed at 6 months for patients undergoing RFA.

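### The adverse-event classes leave day 91 to month 6 and all time after month 12 without a class, and the plan does not say whether safety reporting survives the below-1:1 closure rule

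*Protocol article*

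**What the plan says.** The Toxicity evaluation section introduces its classes with "The secondary safety endpoints for VT-ART include the evaluation of all adverse events, which are classified as follows". Three follow:

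- "Acute, during the patient’s hospital stay"
- "Subacute, in the first 90 days from discharge"
- "Chronic, 6–12 months following discharge"

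The same section makes two further commitments: "All adverse events, regardless of the toxicity grade and all-cause mortality, will be reported in the final study", and "Patients will be re-evaluated at 2 years of follow-up for late-onset toxic effects".

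The Follow-up section uses a different starting point: "Follow-up will be conducted for 36 months after treatment administration". Its visits (ECG and echocardiography at 3, 6 and 12 months, ICD interrogation at 6 to 36 months) are likewise timed from treatment.

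The accrual rules at the end of the Sample size section contain the closure rule: "The final analysis will not be performed at all if less than a 1:1 ratio" of controls to VT-ART patients has been reached. In that case the study is closed.

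**The concern.** A classification meant to hold every adverse event should have a place for each one. This list has none for an event in month 4 or 5 after discharge, or for anything after month 12. The findings of the planned 2-year toxicity review therefore fall outside every class of the safety endpoint that the same section defines. The first gap also nearly coincides with the period (the 4th to 6th month after the procedure) in which VT burden is counted for efficacy. For those months, benefit would be tabulated while harm had no class.

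The closure rule raises a related but separate question. It depends only on how many controls are found, which says nothing about harm in patients already irradiated. Neither it nor any other section says that VT-ART safety would still be reported if the study closed. Safety is a stated aim, so the plan should not leave this to interpretation.

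**Working it through.** **Windows.** The inputs are the three windows in Toxicity evaluation, with one month taken as 365.25/12 = 30.44 days.

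| Time after discharge | Class |
|---|---|
| Hospital stay | Acute |
| Day 0 to 90 | Subacute |
| Day 91 to month 6 (day 182.6) | None |
| Month 6 to 12 (day 182.6 to 365.25) | Chronic |
| After month 12 | None |

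- First gap: 6 × 30.44 − 90 = 182.6 − 90 = 92.6 days, or 3.0 months.
- Share of the first year after discharge: 92.6 / 365.25 = 25%.
- Second gap: from month 12 to the end of follow-up at month 36, about 24 months. The 2-year review lies inside it. The figure is approximate because the class ends 12 months after discharge, while follow-up ends 36 months after treatment.

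**Clocks.** Let L be the days from treatment to discharge, which the article does not give. The 6-month visit, timed from treatment, falls 182.6 − L days after discharge. The chronic class opens at 182.6 days. For any L above zero, an on-schedule 6-month echocardiogram therefore comes before the chronic class opens, and an event dated to that visit falls in the first gap.

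**Closure rule.** The inputs are the 49 planned VT-ART patients and the 1:1 threshold. With 49 VT-ART patients, 48 controls give 48/49 = 0.98 and trigger the rule; 49 controls do not. The accrual check starts only once the planned VT-ART number has been collected, so the full VT-ART group would already exist when the rule was applied.

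**What a VT-ART-only safety report would hold.**

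- With 49 patients and no event of a given type, the one-sided 95% upper limit is 1 − 0.05^(1/49) = 5.9%.
- If the true rate were 5%, the chance of seeing at least one event is 1 − 0.95^49 = 92%.
- With 44 patients (49 less the plan's 10% drop-out), the same figures are 6.6% and 90%.

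Such a report would therefore be informative without any controls.

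**The case against.** **Unclassified is not unreported.** The section promises to report every adverse event of any grade, and all-cause mortality. This stands. A reader might infer that events in the gaps would be lost, but the text does not support that. The defect is confined to class-wise tabulation.

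**Most of the unclassified time lies after month 12.** Adding both gaps gives 3 + 24 = 27 of 36 months, and a reader might take that to mean that safety goes unassessed for three quarters of follow-up. It does not. The sum subtracts windows counted from discharge from follow-up counted from treatment. It measures calendar time, not events, and 24 of the 27 months lie after month 12, where the 2-year review is provided. The firmer figure is the 3-month gap in the first year.

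**The Discussion does not define this trial's harms.** It lists pericardial effusion, pericarditis and pneumonitis as effects seen in earlier studies. It neither makes them endpoints here nor gives timings that place them in the gaps.

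**The closure rule may concern only the matched comparison.** It stands under the statistical considerations for the matched-pair analysis, shortly after the final analysis is described as whole-group and subgroup comparisons by matching level. Adverse events have their own heading. A reader might infer that the rule flatly contradicts the reporting promise, but no sentence says that safety reporting stops. What remains is an ambiguity: the ban is absolute, the study is closed, and no exception is given. The rule also applies only after two safeguards have failed, namely relaxation to the mandatory matching factors and the use of retrospective controls from up to 5 years back.

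**Some choices are legitimate.** An in-hospital acute class, and declining to run an under-matched comparison, are defensible decisions and are not disputed here.

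**An article condenses.** That excuses missing detail. It does not excuse windows that are stated in full and fail to meet.

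**Conclusion.** The point holds for the windows, with high confidence. About 3 months of the first year after discharge (25%) and all time after month 12 have no class, although the list is introduced as covering all adverse events and the plan looks for late toxicity at 2 years. Subacute and chronic rates tabulated as written would omit events in those periods, even though the events themselves are promised in the report. The 3-month figure rests only on the stated windows and an average month length. The length of the second gap also depends on the unstated interval between treatment and discharge, and changes little if that interval is short.

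On the closure rule the conclusion is weaker. The documents leave open whether VT-ART safety is reported if the study closes below 1:1. They do not establish that it would be withheld. The plan should be clarified on this point.

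**What to change.** 1. Replace the three classes with contiguous windows on one clock starting on the day of VT-ART. For example: up to day 90 (with the in-hospital part shown separately), day 91 to month 12, and beyond month 12 to the end of follow-up.
2. State how events after month 12 are ascertained. From then on, the Follow-up section lists only ICD interrogations, and toxicity rests mainly on the 2-year review. The last class should be reported with that limit stated.
3. Add a sentence to the accrual rules saying that the below-1:1 rule applies to the matched comparison only, and that VT-ART safety and descriptive outcomes are reported in any case.

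Items 1 and 3 cost wording and a little extra tabulation. They change no treatment, visit or sample size. Item 2 may need a short ascertainment rule, because it is not shown that events after month 12 are collected systematically outside the 2-year review.
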